## Abstract

**Background:**

As the number of people living with dementia grows, so does the need to provide them with adequate psychosocial support. Many people with dementia live at home with family carers, who also require social and emotional support to cope with their role. Community group singing has received attention for its potential to support people with dementia and their carers. It is postulated that singing can improve cognitive function, strengthen the bonds between care partners and help to establish social support networks. However, there is a lack of rigorous evidence of singing’s benefits for this population. This study aims to test the feasibility of a randomised controlled trial of community singing in dementia, to pave the way for a larger, conclusive study.

**Methods:**

The PRESIDE study is designed as a two-arm, parallel-group randomised trial with a waiting list control. Dyads consisting of a person with dementia (*n* = 80) and their carer (*n* = 80) will be recruited. Each dyad will be randomised either to attend 10 weeks of community group singing sessions straight away or to wait for 3 months before attending the sessions. The singing sessions will be led by experienced professional musicians and will last about 90 min, including time for socialising. The primary outcome of this study is the attainment of feasibility criteria around recruitment, retention and the acceptability of the waiting list control. Secondary outcomes include the quality of life, mood, cognition, and musical engagement of the person with dementia, and quality of life, mood, and experiences/challenges of the carer. These data will be collected during home visits at baseline, and 3 and 6 months post-baseline.

**Discussion:**

Despite growing public interest in the positive effects of singing, and encouraging findings from qualitative and non-randomised quantitative studies, there is a lack of rigorous evidence. This is the first randomised controlled trial of community group singing for people with dementia in Europe, to our knowledge. If the results favour a full trial, conclusively demonstrating the effectiveness of group singing could positively affect the opportunities available to community-dwelling people with dementia and their carers.

**Trial registration:**

Unique identification number in ISRCTN registry: ISRCTN10201482. Date registered: 12 May 2020

## Introduction

### Background and rationale

As our population ages, the number of people living with dementia is set to increase, with an estimated 2 million people predicted to have the condition in the UK by 2050. Although dementia is progressive, people may live for many years after diagnosis. Residential care is an option for those with higher needs, but the majority (61%) of people with dementia live in the community, many supported by family carers [1]. People with dementia are at greater risk of loneliness and mental health problems than the general population [2, 3]. Although many family carers find their role rewarding, caring responsibilities can incur a significant psychological and physical strain. Unless they are well resourced and supported, carers may find themselves at heightened risk of depression and anxiety, and consequently with poor quality of life [4]. If caregivers experience unalleviated and overwhelming challenges in their role, this may result in earlier admission to residential care for the person with dementia, leading to a lower quality of life for them and increased pressure on social care services [5].

Consequently, there is a need for psychosocial interventions, which support people with dementia and their carers to live well with the condition for as long as possible. One such intervention is cognitive stimulation therapy (CST), which can improve cognition and quality of life for people with dementia and is recommended by the National Institute for Health and Care Excellence (NICE) for all people with mild or moderate dementia [6, 7]. Community group singing is growing in popularity as an activity to support the mental well-being of people with dementia and their carers. There is evidence from neuropsychology that singing provides cognitive stimulation through multiple effects on the brain, but that response to singing is mediated by clinical and demographic factors [8]. A randomised trial compared the effects of singing, listening to music and usual care for person with dementia/carer dyads, and found that both singing and listening to music improved mood, orientation and remote episodic memory, whilst singing also improved carer well-being [9]. Qualitative evidence indicates that singing for people with dementia has a positive effect on the relationship between couples when one partner has a diagnosis of dementia [10] whilst a study of group singing in the general population has indicated that it may accelerate social bonding [11]. Participants at singing groups for those with dementia have also reported that they find the support network provided by meeting other people in a similar situation very helpful [12]. Meanwhile, there is evidence from a randomised controlled trial that group singing is a cost-effective way of improving quality of life and reducing anxiety and depression for people over the age of 60 [13].

Despite the growing interest in group singing for people with dementia, there is a lack of conclusive evidence about its effects. To date, no published large-scale, randomised study has evaluated group singing for people with dementia and their carers in the community. A study of this kind has recently been completed in Australia (Australian and New Zealand Clinical Trials Registry (ANZCTR) ID: ACTRN12617001513303) and the results are pending publication (this study has singing groups facilitated by music therapists whilst the facilitators in the present study are community musicians, so this will make an interesting point for comparison). Evidence from smaller studies is variable; several studies found no change on standardised measures of quality of life, mood, or neuropsychiatric symptoms of dementia, but reported favourable qualitative findings [14–16]. In a small pre-post study of group singing which showed improvements in quality of life, self-esteem and social support for people with dementia and their carers, the authors call for an evidence base to demonstrate the psychological benefits and potential for improvement in cognitive function which they believe group singing affords [17]. Therefore, there is an identified need for rigorous RCT evidence to isolate the effects of group singing for people with dementia and their carers. Such evidence could inform health and social care policy, help to secure additional funding for group singing and potentially reduce the pressure on health and social care services by improving support for people living with dementia in the community and their carers.

### Study objectives

The primary objective of the PRESIDE study is to test the protocol for a two-arm, parallel-group superiority randomised trial of community singing in dementia with a waiting-list control design. The relevant indicators are recruitment, retention, and the acceptability of the trial designs to the participants, including the waiting-list control. The rationale for the waiting list design is that a control group, which only receives care as usual, would be likely to experience resentful demoralisation with attendant drop-out. If the results of this feasibility study are favourable, a full-scale trial would aim to recruit 360 dyads, sufficient to identify a moderate effect size on quality of life (0.3) [13, 18].

The secondary objective of the study is to explore the impact of group singing on people with dementia and their carers, using quantitative and qualitative methods. It is anticipated that this data will indicate suitable outcome measures for the full trial, and improve our understanding of the mechanisms of action at play in group singing for people with dementia.

## Methods

### Study design

This feasibility study is designed as a two-arm, parallel-group randomised controlled trial of community singing for people with dementia and their carers, with a waiting-list control group. The study will aim to recruit 80 dyads each consisting of a person with dementia and their carer. About half of the sample, selected at random, will be invited to attend a singing group, whilst the other half will be asked to wait for 3 months before being invited to attend a group. Outcome data will be collected at baseline (time 0), 3 months after baseline (time 1), and 6 months after baseline (time 2).

### Setting

The singing groups created for the study will take place in community settings in Nottinghamshire, UK, and data collection will take place during visits to participants at home. The venues selected will be chosen for their suitability for holding singing group sessions; this means well-lit, attractive spaces with good acoustics that are large enough to comfortably accommodate up to 50 people. Further considerations include the provision of accessible facilities and a kitchen for refreshments, adequate car parking and a reliable and frequent public transport service nearby. We will focus on two geographical areas and will aim to recruit half the intended target of 80 dyads in each of these areas. Recruitment will be optimised by selecting venues in geographical areas that are believed to have the highest levels of need in terms of the provision of recreational singing for people with dementia.

### Inclusion and exclusion criteria

To be included in the study, participants with dementia must
Be aged 18 or over, and diagnosed with dementia, which is at a mild or moderate levelHave a carer who spends at least 2 h per week with themBe able to give informed consent at the start of the studyBe able to speak and understand English^1^Be willing in principle to join a singing group and attend weekly

Participants with dementia will be excluded if
They lack capacity to give informed consentThey are already attending a singing group or have done so in the past 6 weeks (other than religious services)They have a significant hearing impairmentThey are already participating in any other interventional studyThey have a history of severe mental illness or drug/alcohol addiction

Carers can be included if they are
Able to speak and understand EnglishWilling in principle to attend the group weeklyAble to give informed consent

Relationships between people with dementia and their carers may be that of spouses/partners, parent/child or other family members, or friends. In certain cases, professional caregivers may be part of the study if no family member or friend is available to accompany a person with dementia to the sessions and if the same professional caregiver is available each week. The nature of the relationship between the dyads does not matter, but it is important that the same carer attends the sessions throughout the study.

### Intervention

The intervention in this study is attendance at weekly singing group sessions for 10 weeks. Each session will include approximately 60 min of warm-up activities and singing, with about 30 min for refreshments and socialising before or after the session. The sessions will be run jointly by two professional community musicians who have extensive experience of running similar singing groups together. The format of the sessions includes a full physical and vocal warm-up, followed by singing familiar songs accompanied by guitar. Themed songbooks will be provided for participants; each week a different songbook will be selected by the facilitators, so each session will have a different theme. Themes might include songs about the weather, from a particular era, or relating to the current season (e.g. Christmas, summer). Singing group participants will be encouraged to choose their favourite songs from the books for the whole group to sing. The facilitators’ approach will emphasise that the aim of the group is to sing for fun and enjoyment, and that the participants’ musical skills or singing voices are not being assessed or judged.

The content of each session will be fully documented, and three out of every ten sessions will be video recorded in order to check that the intervention is delivered consistently. Attendance at singing sessions will be monitored and recorded. Participants will be free to miss individual sessions or withdraw from the singing group entirely as they wish, and they do not need to give a reason.

Since each singing group can accommodate up to 20 dyads, we propose to run four groups in total in two different geographical areas. The first two groups will be set up for those allocated to the intervention group; after the 3 month waiting period, we will start another two groups for those in the waiting-list control group. There is provision for those in the intervention group to continue to attend the singing groups after the initial 10-week period, if they wish to. This is for ethical reasons and to facilitate embedding the groups into the local community, as discussed later in the “Ethics and dissemination” section. Continued attendance by participants in the intervention group will not compromise the primary objectives of recruitment, retention and acceptability, and its effects on the 6-month data collection are considered an acceptable trade-off.

### Control condition

Participants who are allocated to the waiting-list control group will receive care as usual during the 3 months that they will be required to wait before beginning to attend a singing group. They will be requested to abstain from attending other organised group singing activities during this time, with the exception of religious services.

### Endpoints

Since PRESIDE is a feasibility study, the endpoint is the attainment of the feasibility criteria at 6 months. The proposed criteria for proceeding to a full trial are 70% recruitment; 70% retention of participants over 3 months; and acceptability of the control condition demonstrated by 70% of the waiting-list participants starting singing groups after being on the waiting list. The acceptability of the control condition is considered to be the most important of these three criteria since this ensures the heterogeneity of the sample. The other feasibility criteria are considered negotiable.

An additional endpoint for PRESIDE is the measurement of quality of life, activities of daily living, mood, musical engagement and cognition of people with dementia, and the measurement of quality of life, mood, caring relationship and experience of caring for the carers of the people with dementia. Each dyad’s use of health social care services and resources will also be documented. Additionally, qualitative data will be collected using interviews and participant observation, in order to better understand the experiences of dyads who attend the singing groups.

### Participant timeline in study

Figure 1 shows the timeline of participants in the study, whilst Fig. 2 gives the schedule of assessment and enrolment for the study. Since we need to recruit a sufficient number of participating dyads before the singing groups can begin, there will be a delay between recruitment and beginning the singing group or waiting list control for participants who are recruited early. We will not collect baseline data or randomise participants until the singing groups are just about to start.

**Fig. 1 Fig1:**
[figure not shown]
Participant timeline in study

**Fig. 2 Fig2:**
[figure not shown]
Schedule of enrolment, intervention and assessment for PRESIDE

### Sample size

As PRESIDE is a feasibility study with two arms, it is suggested 40 dyads per arm will provide enough information to inform future, definitive RCT design and implementation [19]. Therefore the recruitment target is 80 patient-carer dyads in total in the current study.

### Allocation and blinding

Participants will be recruited in pairs consisting of a person with dementia and a carer. They will be randomised in pairs to either the intervention group or the waiting-list control group. Randomisation will be stratified by sex and Clinical Dementia Rating (CDR). Randomisation will be carried out using a web application created by the trial programmer at the University of Nottingham Stroke Trials Unit, using web and database servers provided by University of Nottingham Information Services (IS). The researcher (BD) will use this web application to randomise each participant. The system will hide information relating to the intervention groups from other users until explicitly granted access by the trial programmer, for example, when a statistician requires unblinded data.

Dyads will be randomly allocated to intervention or waiting-list control groups by the web-based system. BD will collect baseline data prior to randomisation, and so will be unaware of allocation until the initial data collection is complete. Thereafter, both the researcher (BD) and the participants will be aware of the group allocation, along with those delivering the sessions. Due to the nature of the intervention and control groups, it is not feasible to blind participants to group allocation; they will know whether they are attending singing group sessions. The research team will be split into two groups, which will define their access to data and to group allocation. The data management group will be responsible for the data collection and running of the study, and will not be blinded to group allocation once baseline data collection has taken place. The data analysis group will be responsible for conducting the analysis, and will remain blinded to group allocation for the duration of the study. The data analysis group will not have any contact with study participants.

Follow-up data collection will be undertaken by researchers who are blinded to group allocation. However, since the participants will know their own group allocation, there is a possibility that they will reveal this during the follow-up data collection. Unblinding of outcome assessors which occurs in this way will be recorded. All researchers undertaking data collection will have been fully trained in the administration of these instruments.

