### Data coding and analysis

#### Statistical analysis of quantitative data

Quantitative data analysis will be conducted by the study statistician (BG), using the software package Stata 16. The data analysis will be mainly descriptive [38]. All measures will be summarised with mean and standard deviation (S.D.) for normally distributed variables, median and inter-quartile range (IQR) for skewed variables, and frequency (%) for response of categorical variables, by intervention arm across follow-up time. Analysis of Co-variance (ANCOVA) will be performed to quantify treatment effect size and its precision by means of regression modelling with baseline measures as covariate, and to derive the change from baseline score for each arm. Due to the non-independence of patient-carer dyad measures and with data being measured repeatedly, multivariate, multilevel modelling will be performed to account for the association between the same kind of outcome measure of patient-carer data and repeated data. We will calculate recruitment rate, retention rate and attrition rate, exploring patterns of missing data and drop out from the intervention group and the waiting list control group. All results will be used to inform future definitive trial design.

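### The stated ANCOVA names no randomisation stratifier, and allocation is not balanced by area although group places exactly equal the target

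*Protocol article*

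**What the plan says.** Three parts of the protocol article bear on this.

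- **Allocation and blinding:** "Randomisation will be stratified by sex and Clinical Dementia Rating (CDR"). No other factor is named.
- **Statistical analysis of quantitative data:** treatment effect size and precision are to come from ANCOVA, "by means of regression modelling with baseline measures as covariate". A further model is planned: "multivariate, multilevel modelling will be performed to account for the association between the same kind of outcome measure of patient-carer data and repeated data". Neither description names sex, CDR as a stratum, or area. The same section says "The data analysis will be mainly descriptive".
- **Setting and Intervention:** "We will focus on two geographical areas and will aim to recruit half the intended target of 80 dyads in each of these areas". On groups: "Since each singing group can accommodate up to 20 dyads, we propose to run four groups in total in two different geographical areas". Two of these serve the intervention arm from the start, and two more open after three months for the waiting-list arm.

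The participant timeline section delays baseline collection and randomisation until the groups are about to start. The Discussion describes waiting for about 40 dyads before the first group, then dividing them roughly in half.

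**The concern.** Stratifying makes the arms more alike on sex and dementia severity than chance would. A model that ignores those factors leaves their contribution in the residual and does not credit the design with the balance it created. The reported standard error then exceeds the true one. The article says all results will inform the definitive trial, so precision estimates that are too wide would carry forward.

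Area raises a different issue. It determines which venue and group a dyad can join. Four groups of 20 give 80 places for a target of 80, so at full recruitment every area must split exactly 20/20 to fit. Nothing described protects that split. Unequal splits would also mix some of any difference between areas into the arm comparison.

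**Working it through.** **Target and capacity.** Sample size: 2 arms × 40 dyads = 80. Intervention: 4 groups × 20 dyads = 80. Setting: 80 / 2 areas = 40 per area, and one group per arm in each area gives 2 × 20 = 40 places. The target is reproduced and capacity has no slack.

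**Standard error without the stratifiers.** Let R² be the share of the variance left after baseline adjustment that sex and CDR explain. With perfectly balanced strata, model SE / true SE is about 1/√(1 − R²). At R² = 0.10 this is 1/√0.90 = 1.05, and at 0.20 it is 1/√0.80 = 1.12. Incomplete blocks leave some imbalance, so simulated values are slightly lower. The simulation used 80 dyads, four sex × CDR strata, blocks of 4 and a baseline-outcome correlation of 0.5. Block size, the two CDR levels, the correlation and R² are assumptions, as the article gives none of them.

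| R² | Model SE / true SE, baseline only | Null rejection at nominal 5% | Ratio with sex and CDR added |
|---|---|---|---|
| 0 | 1.00 | 4.7% | 1.00 |
| 0.02 | 1.00 | 5.1% | 0.99 |
| 0.05 | 1.03 | 4.3% | 1.00 |
| 0.10 | 1.04 | 3.8% | 0.99 |
| 0.20 | 1.11 | 3.1% | 1.00 |

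A second simulation gave about 3% and 10% excess at R² = 0.10 and 0.20. With adjustment, the null rejection rate is 4.7-5.4%.

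**Split within an area at full recruitment.**

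- Simple randomisation of 40 dyads: P(not 20/20) = 1 − C(40,20)/2⁴⁰ = 0.875 for one area, and P(22 or more in one arm) = 0.636.
- Arms fixed at 40/40 overall but blind to area (hypergeometric): 0.823 above 20, and 0.117 at 24 or more.
- Permuted blocks within sex × CDR (blocks of 4 or 6, two or three CDR levels, all assumed), chance that at least one area is affected:

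| Order of randomisation | Above 20 | 22 or more | 24 or more |
|---|---|---|---|
| Areas mixed | 0.92-0.95 | 0.61-0.66 | 0.16-0.19 |
| One area after the other | 0.81-0.90 | 0.26-0.48 | 0.005-0.055 |

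**Sensitivity to recruitment.** Chance that any group exceeds 20, with blocks of 4 and two CDR levels:

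| Dyads per area | Areas mixed | One after the other |
|---|---|---|
| 40 | 92% | 81% |
| 38 | 59% | 26% |
| 36 | 31% | 5% |
| 34 | 13% | 0.4% |
| 28 (70% of target) | 0.1% | 0% |

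**Effect of an area imbalance on the arm contrast.** With splits of 22/18 and 18/22, one area supplies 22/40 = 0.55 of one arm and 18/40 = 0.45 of the other, a difference of 0.10. An assumed area difference of 0.2 SD then shifts the arm contrast by 0.10 × 0.2 = 0.02 SD.

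**The case against.** The strongest objection to the ANCOVA half is that a journal article condenses the analysis. A full covariate list commonly sits in the analysis plan. The plural in "regression modelling with baseline measures as covariate" could already take in CDR, which is measured at baseline, and sex is recorded then too. This stands, and it limits confidence that the stratifiers are really left out. It does not remove the value of naming them.

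A reader might go further and infer that the standard errors are wrong whatever the data, or that the trial's conclusions lose validity or power. The documents do not support that. The error exists only if the strata are prognostic beyond baseline, and for cognition or daily living the baseline score may already carry much of severity. It widens intervals and never narrows them. The analysis is mainly descriptive, and the 360-dyad figure for the full trial rests on a cited effect size of 0.3, not on this standard error.

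On area, the objection is that the high overshoot probabilities belong to exact full recruitment. The article reports slower recruitment than hoped, sets its own bar at 70%, and appears to randomise in batches. Waiting-list groups also fill only with dyads who still want to start. Venues are to hold up to 50 people, and 23 dyads with two facilitators make 2 × 23 + 2 = 48. All of this stands: the overshoot is usually small and vanishes with modest under-recruitment.

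A reader might also infer that the cap could spoil the waiting-list criterion, or that site imbalance biases the comparison. With 24 dyads in a waiting-list group held strictly to 20 places, 20/24 = 83% could still start, above the 70% threshold. Area imbalance under randomisation is chance, not bias. At three months only the intervention arm has attended groups, so stratifying by area would not remove group effects.

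**Conclusion.** The point holds in a limited form, with medium confidence.

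- **Covariates.** The ANCOVA as stated does not name the factors used to stratify. If it is run that way, the standard error is overstated by about 0-4% when sex and CDR explain up to 10% of the residual variance, and by about 10% at 20%. The documents give no such share, so this is an assumed range. The direction is conservative.
- **Area.** Allocation is not balanced by area although places equal the target, so at full recruitment the exact 20/20 split in each area is unprotected. Some excess over 20 is then likely (81-95% under the assumed blocks). It is usually a few dyads, and with areas randomised in turn the chance is about 5% at 36 dyads per area.

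Neither part affects how the feasibility criteria are calculated. The changes are worth making because they cost almost nothing and recruitment was paused when the article was written.

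**What to change.** 1. State that the ANCOVA and the multilevel model include sex, CDR (as used for stratification) and area as fixed covariates alongside the baseline value of the outcome. This costs one sentence and a few degrees of freedom out of 80 dyads.
2. Balance allocation within area. One way that fits the existing timetable is to randomise each area's batch 1:1 once its baselines are complete, with balance on sex and CDR. A batch of 40 then splits 20/20 and fits the stated capacity. Adding area as a further stratifier in the web tool is an alternative, but it doubles the number of strata and incomplete blocks can leave the split slightly uneven.

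The cost is a setting in the randomisation tool and a short delay before dyads learn their allocation.
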